#### System utility evaluation

##### Patient evaluation

Patients will complete periodic online progress evaluation surveys following the completion of their third, sixth and ninth PROMPT-Care assessments. Patients will be asked about the usability of the system, preferences for timing of completing PROMPT-Care assessments, satisfaction and usefulness of the system, suitability and value of the self-management materials, and suggestions for further refinement. A sub-set of patients (approximately 10–20 patients) will also be invited to participate in semi-structured interviews at study completion in order to further explore themes identified in the evaluation surveys.

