### Objective

The overall objective of this study is to implement the PROMPT-Care 2.0 eHealth platform and determine its efficacy among cancer patients at four tertiary hospitals. Specifically, this study will test whether web-based routine collection of PROs, combined with automated alerts to clinical teams and provision of patient self-management resources, result in reduced emergency department presentations, and improved chemotherapy delivery and health service referrals. The study will also evaluate system utility and potential benefits and barriers to PROMPT-Care implementation in routine care from both the patient and healthcare professional perspective.

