##### In clinic

Eligible patients attending a cancer care clinic will be invited to participate by a member of the clinical trial team in the waiting area. The trial research member will explain the study in detail and provide patients with a study pack containing a letter of invitation, participant information and consent form, demographics survey and reply-paid envelope. Consenting patients will be asked to complete a consent form and their first PROMPT-Care assessment just prior to their appointment.

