#### Assessment completion

Patients will complete PROMPT-Care assessments on a monthly basis and will be followed up for a minimum of four months. Patients will have the option to complete assessments either at the hospital in clinic, their home or any public community location. Patients completing assessments in clinic will be provided with a tablet device in the waiting area just prior to their scheduled appointment. Patients who complete assessments from home or in community locations will receive an email containing the survey link three days before their assessment is due.

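### Patient evaluation surveys go out only after the third, sixth and ninth completed assessments, so the survey results leave out patients who stop before the third

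*Protocol article*

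**What the plan says.** Under Patient evaluation, the protocol article fixes when patients are surveyed: "Patients will complete periodic online progress evaluation surveys following the completion of their third, sixth and ninth PROMPT-Care assessments". On content it says "Patients will be asked about the usability of the system, preferences for timing of completing PROMPT-Care assessments, satisfaction and usefulness of the system"; the survey also covers the self-management materials and suggestions for refinement. The same section adds interviews: "A sub-set of patients (approximately 10–20 patients) will also be invited to participate in semi-structured interviews at study completion", with the purpose given as "in order to further explore themes identified in the evaluation surveys".

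The Objective section says the study will "evaluate system utility and potential benefits and barriers to PROMPT-Care implementation in routine care", from both the patient and the professional side. Under Assessment completion, "Patients will complete PROMPT-Care assessments on a monthly basis and will be followed up for a minimum of four months". For in-clinic recruits, "Consenting patients will be asked to complete a consent form and their first PROMPT-Care assessment just prior to their appointment".

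Other sources feed the utility evaluation. There are surveys and interviews of oncology staff and GPs (Healthcare professional evaluation). There are also usage data and an error log that includes technical problems reported by patients (System usage statistics).

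**The concern.** The trigger is a completed assessment, not elapsed time. The survey asks about ease of use, usefulness and timing, and each of these is a plausible reason to stop. Whether a patient is surveyed may therefore depend on the answer that patient would have given. A patient who gives up after one or two assessments is not counted as a non-responder; no survey is ever due.

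What is at stake is the utility evaluation. The Discussion section says the results will guide revision of the system and its wider roll-out. If those who found the system hard to use or irrelevant are missing, the surveys will probably look more favourable than patient experience as a whole, and reasons for stopping will be under-recorded.

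**Working it through.** **Inputs from the article.** Surveys follow completed assessments 3, 6 and 9 (Patient evaluation). Assessments are monthly with at least four months of follow-up (Assessment completion). In-clinic recruits do the first at consent (In clinic). The minimum intervention group is 352 (Sample size). No attrition rate and no satisfaction figure is given.

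**The plan's own figure.** There is no stated figure for survey coverage to reproduce. The 352 serves only as a denominator. It is close to a two-sided 5%, 80% power calculation on the Poisson log rate ratio: (1.960 + 0.842)² × [1/(1.4 × 0.86) + 1/(4 × 1.4)] / (ln 0.86)² = 348.2, so 349 per intervention arm. Nothing below depends on that calculation.

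**Timing.** With the first assessment at month 0, assessment k falls at month k − 1. Assessments 3, 6 and 9 fall at about months 2, 5 and 8. A patient followed for exactly four months can complete assessments at months 0, 1, 2, 3 and 4, which is five, and so cannot reach the second survey however adherent. The article does not say when mail-out recruits do their first assessment.

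**Share not surveyed.** Assume that all 352 complete the first assessment, that a constant proportion q stops for good between successive assessments, and that follow-up is long enough to reach each wave. Then:

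- share never surveyed = 1 − (1 − q)²
- share reaching survey 2 (assessment 6) = (1 − q)⁵
- share reaching survey 3 (assessment 9) = (1 − q)⁸

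| q (assumed) | Never surveyed | Of 352 | Reach survey 2 | Reach survey 3 |
|---|---|---|---|---|
| 5% | 1 − 0.95² = 9.8% | 34 | 77% | 66% |
| 10% | 1 − 0.90² = 19% | 67 | 59% | 43% |
| 20% | 1 − 0.80² = 36% | 127 | 33% | 17% |

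**Effect on a satisfaction percentage at the first survey.** Overstatement = share never surveyed × (satisfaction in those surveyed − satisfaction in those not surveyed). Both satisfaction levels are assumed. With 85% among the surveyed:

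- 9.8% never surveyed, 70% of them satisfied: 0.098 × 15 = 1.5 points
- 25% never surveyed, 50% of them satisfied: 0.25 × 35 = 8.75 points (0.75 × 85 + 0.25 × 50 = 76.25%)
- 36% never surveyed, 50% of them satisfied: 0.36 × 35 = 12.6 points

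If those who stop are as satisfied as those who continue, the overstatement is zero. These figures show how the bias would scale; they do not estimate it for this trial.

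**The case against.** The case for the plan has real substance.

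- **Timing.** Clinical alerts and second-tier resources arise only after a threshold is breached at two consecutive assessments. Assessment 3 is therefore the first that can follow exposure to both. This is a sound reason for the timing, and the fix keeps it. It is not a reason to make the survey conditional on completing the assessment.
- **Other sources.** A reader might infer that early stoppers are never heard at all, or that the whole utility evaluation rests on those who persist. The article does not support this. Anyone who stops after the third assessment has been surveyed at least once. The interviews are not stated to be limited to survey responders. The error log, usage data, and staff and GP evaluations do not depend on a third assessment. These sources offset the gap only weakly: the interviews are few, come at the end and take their themes from the surveys; the log records technical faults rather than reasons for stopping; and professionals do not supply the patient's view.
- **Change across waves.** A reader might also infer that the trial will report a spurious rise in satisfaction from the first to the last survey. No comparison between waves is planned, so this is only a caution for anyone who reads the waves as a trend.
- **Late recruits.** Calendar months 6 and 9 are just as far out of reach for a patient followed for four months. This is not a fault of the trigger; it is dealt with by reporting the right denominator.
- **Direction and size.** Patients also stop through illness or death, so upward bias is probable rather than shown.
- **Condensed article.** Withdrawal procedures and interview sampling may be set out in a fuller protocol, and their absence here is not the finding. The finding is the survey trigger, which the article states.

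**Conclusion.** The point holds for the survey part of the patient evaluation. Patients who stop before the third assessment, about month 2 for in-clinic recruits, receive no survey, and later waves come from increasingly adherent patients. Survey-based usability and satisfaction results are open to selection bias, probably upward, in a study that means to assess barriers from the patient's perspective.

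The size is unknown. The range of about 10% to 36% of 352 patients never surveyed rests on an assumed 5% to 20% stopping between monthly assessments, at a constant rate and for good. The size of any bias further depends on how far those who stop differ in their views, on which the article gives nothing.

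The primary outcome and the secondary outcomes (time on chemotherapy, allied health referrals) are extracted from the electronic medical record and the oncology information system, so they are not affected. This is a cheap improvement, not a threat to the trial's main conclusion.

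**What to change.** 1. Send the existing online survey when the third, sixth and ninth assessments fall due, completed or not, to every patient still enrolled.
2. Send a short version at withdrawal, or when a patient lapses under a rule set in advance. Step 1 alone would still miss those who have formally withdrawn.
3. Report each wave against the number of patients whose follow-up could have reached it, with the number who responded.
4. Include some early stoppers among the 10 to 20 interviews already planned, and let those interviews cover reasons for stopping as well as survey themes.

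The main change is to an e-mail trigger, since the system already e-mails assessment links to patients who complete them outside the clinic. The costs are a lower response rate, because non-users will answer less often, and a small extra burden on patients who withdraw. Non-response among early stoppers would at least become visible.

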##### Healthcare professional evaluation

Participating oncology staff and GPs will be invited to participate in evaluation surveys and semi-structured interviews at study completion. Oncology staff will be asked questions about, how they used the PROMPT-Care reports in clinical practice and their usefulness, their response to the clinical alerts, how PROMPT-Care impacted routine care, and their views on the Treatment Summary and SCPs. GP data will be analysed to evaluate the content and suitability of the Treatment Summary and SCPs. It will also be used to gauge attitudes towards shared-care models of survivorship care planning.

##### System usage statistics

Data on the use of the PROMPT-Care system will be extracted from the OIS and evaluated to inform: frequency of report usage, clinical alert activity, assessment data transfer, and IT system functioning. User and technical system errors will also be monitored by research staff and recorded in an error log of IT issues and associated resolutions e.g. firewall upgrades, server downtime, participant report of IT problems completing assessments or accessing resource webpages. Patient interaction with and use of the self-management resources will be analysed by Google Analytics [22] and ClickMeter [23] over time. Google analytics will be used to gather data on the number of users and views of the domain-specific resource webpages (eg. emotional, physical, social/family, maintaining well-being, and practical problems), whereas ClickMeter will be used to track clicks into the individual resources (*n* = 114), sitting within each domain page. System usage data will be summarised using simple descriptive statistics and will be presented as counts, mean scores, standard deviations and percentages.

### Sample size

A minimum sample size of 1760 (352 intervention and 1408 control) patients is required to detect a 14% reduction in the number of ED presentations in the PROMPT-Care group compared with the control group. This is based on the assumed rate of ED presentations being 1.4 visits per patient during the study period, a 1:4 ratio of PROMPT-Care to control group patients, 80% power and 5% statistical significance.

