**Methods:**

Groups eligible to participate in the intervention arm of this controlled trial are patients receiving cancer care (including follow-up). PROMPT-Care patients will complete monthly assessments (distress, symptoms, unmet needs) until voluntary withdrawal or death. In Version 1.0, the care team accessed patients’ clinical feedback reports in ‘real time’ to guide their care, and patients received links to support their self-management, tailored to their PRO responses. Version 2.0 was extended to include: i) an additional alert system notifying the care team of ongoing unresolved clinical issues, ii) patient self-management resources, and iii) an auto-populated Treatment Summary and Survivorship Care Plan (SCP). The control population will be patients extracted from hospital databases of the general cancer patient population who were seen at the participating cancer therapy centres during the study period, with a ratio of 1:4 of intervention to control patients.

A minimum sample size of 1760 (352 intervention and 1408 control) patients will detect a 14% reduction in the number of ED presentations (primary outcome) in the PROMPT-Care group compared with the control group. Intervention patients will provide feedback on system usability and value of the self-management materials; oncology staff will provide feedback on usefulness of PROMPT-Care reports, response to clinical alerts, impact on routine care, and usefulness of the SCPs; and GPs will provide feedback on the usefulness of the SCPs and attitudes towards shared-care models of survivorship care planning.

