### Statistical analyses

Descriptive statistics will be generated for all socio-demographic and clinical characteristics, and outcome measures. A multivariable Poisson or negative binomial regression (depending on over-dispersion) will be used to determine whether the rates of ED presentations were different between the PROMPT-Care and control groups adjusting for covariates (such as age, sex, stage of disease, and treatment status). Number of referrals to allied health services will be analysed similarly. Multivariable Cox proportional hazards model will be used to analyse length of time from start to end of chemotherapy adjusting for covariates.

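### The 352 + 1408 sample size has essentially no allowance for over-dispersion, so the stated 80% power for a 14% reduction is not met if the plan's own negative binomial branch is used

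*Protocol article*

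**What the plan says.** The Sample size section states: "A minimum sample size of 1760 (352 intervention and 1408 control) patients is required to detect a 14% reduction" in ED presentations. It then gives its inputs: "This is based on the assumed rate of ED presentations being 1.4 visits per patient during the study period, a 1:4 ratio" of intervention to control, together with "80% power and 5% statistical significance". It gives no dispersion parameter, standard deviation or inflation factor. It also does not say whether the test is one- or two-sided, or to which group the 1.4 applies.

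The Abstract (Methods) makes the same claim without qualification: "A minimum sample size of 1760 (352 intervention and 1408 control) patients will detect a 14% reduction in the number of ED presentations".

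For the primary outcome, the Statistical analyses section says: "A multivariable Poisson or negative binomial regression (depending on over-dispersion) will be used", adjusted for covariates such as age, sex, stage and treatment status.

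**The concern.** A rate alone fixes the variance of a count only if the count is Poisson. The plan names a second possible model, the negative binomial, whose variance is larger, but the sample size paragraph carries no term for it. If the second model is used, the standard error exceeds the planned one and the 80% no longer applies.

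Over-dispersion is plausible from the design. Recruitment aims for similar proportions of patients on active treatment and in follow-up, all tumour types except blood cancers are eligible, and follow-up has a stated minimum of four months but no stated maximum. In such a population some patients may attend ED repeatedly and others not at all.

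At stake is how a null result is read. A reader who relies on the stated power could take it as evidence against a 14% reduction, when the study may have had much less than 80% power to find one.

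**Working it through.** **Inputs.** From the Sample size section: control rate 1.4; rate ratio 0.86, so the intervention rate is 1.4 × 0.86 = 1.204; four controls per intervention patient; 80% power; 5% significance. Assumed here: a two-sided test, and 1.4 as the control rate. The dispersion k is not in the document and is varied below.

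**Step 1: reproduce the stated figure (Poisson).** For a Wald test on the log rate ratio,

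n(intervention) = (1.960 + 0.842)² × [1/1.204 + 1/(4 × 1.4)] / (ln 0.86)²

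- (1.960 + 0.842)² = 7.849 with unrounded quantiles
- bracket = 0.8306 + 0.1786 = 1.0091
- (ln 0.86)² = (−0.1508)² = 0.02275
- n = 7.849 × 1.0091 / 0.02275 = 348.2

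Rounded up, this is 349 + 1396 = 1745, against the stated 1760. The stated figure is reproduced to within 1%.

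Power at 352 + 1408: SE = √(1.0091/352) = 0.0535, and Φ(0.1508/0.0535 − 1.960) = Φ(0.857) = 80.4%.

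**Step 2: room left for over-dispersion.** With negative binomial variance μ + kμ², the bracket gains k × (1 + 1/4) = 1.25k. Exactly 80% power at 352 needs a bracket of 352 × 0.02275 / 7.849 = 1.0202. So k = (1.0202 − 1.0091)/1.25, which is about 0.009.

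**Step 3: power over an assumed range of k.** SE = √[(1.0091 + 1.25k)/352]; power = Φ(0.1508/SE − 1.960).

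| k (assumed) | Control variance/mean, 1 + 1.4k | SE | Power for 14% reduction at 352 + 1408 | N for 80% power |
|---|---|---|---|---|
| 0 | 1.00 | 0.0535 | 80.4% | 349 + 1396 = 1745 |
| 0.1 | 1.14 | 0.0568 | 75.7% | 392 + 1568 = 1960 |
| 0.25 | 1.35 | 0.0613 | 69.2% | 457 + 1828 = 2285 |
| 0.5 | 1.70 | 0.0681 | 60.0% | 564 + 2256 = 2820 |
| 1 | 2.40 | 0.0801 | 46.9% | 780 + 3120 = 3900 |
| 2 | 3.80 | 0.0998 | 32.7% | 1211 + 4844 = 6055 |

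**Step 4: reduction detectable with 80% power at 352 + 1408.** Solve |ln r| = 2.802 × √{[1/(1.4r) + k]/352 + [1/1.4 + k]/1408} for the rate ratio r. The reduction is 13.9% for k=0, 17.5% for k=0.5, 20.4% for k=1 and 24.8% for k=2.

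**Step 5: other readings of the stated inputs.** Since sidedness and the arm for 1.4 are not stated, the k that would make each reading give exactly 352 was found:

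- one-sided 5% test on the log rate ratio: k about 0.23
- 1.4 as the intervention rate, two-sided: k about 0.12
- two-sided test on the rate difference: k about 0.09

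None of these is stated. Even under them, the allowance is small and undisclosed.

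**The case against.** Several stronger readings are tempting, and the document does not support them.

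- *The sample size is an arithmetic error.* It is not. Step 1 reproduces it.
- *The plan itself expects over-dispersion.* It does not say so. The model choice is conditional, and Poisson is one of the two options. If no over-dispersion remains, the design gives 80.4%.
- *The figure can arise only from a Poisson variance.* Step 5 shows other, less natural readings that reach 352 with some dispersion.
- *The study is known to be underpowered, by a known amount.* The relevant quantity is the dispersion left after adjustment. Stage and treatment status would absorb part of the heterogeneity between treatment and follow-up patients. The document gives no k, so the size of the loss cannot be fixed from it.
- *Covariate adjustment adds a specific further loss.* The document supports no particular inflation factor. Adjustment in a non-randomised comparison can cost precision where group and covariates are correlated, but prognostic covariates can also reduce residual dispersion.

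It is also fair to say that the negative binomial option addresses the validity of inference under over-dispersion. The issue is the planned power, not the type I error.

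Two further defences carry less weight. First, 1760 is called a minimum and controls come from hospital databases, so more could be drawn. But extra controls remove only the control part of the variance. At k=0.5, even unlimited controls give SE = √[(0.8306 + 0.5)/352] = 0.0615 and power Φ(0.1508/0.0615 − 1.960), about 69%. Second, an article condenses the full protocol, and a dispersion assumption may be recorded there. That would excuse missing detail. It does not rescue a power figure that the article states outright and that, on the natural reading of its own inputs, holds only with next to no over-dispersion.

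**Conclusion.** The concern holds in a conditional form. On a two-sided 5% test with 1.4 as the control rate, 352 + 1408 is correct for Poisson counts and leaves room for a dispersion of only about 0.009. If the negative binomial branch is used with any dispersion above that, the power for a 14% reduction is below 80%. The direction is certain under this formula. The size depends on k, which is assumed here: the loss is modest at k=0.1 (about 76% power) and severe at k=1 (about 47%). The claim in the Abstract and the Sample size section should therefore not stand without its variance assumption.

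**What to change.** Recompute the Sample size section with the negative binomial variance and a stated residual dispersion. Take that dispersion from hospital ED data if such data are available. The article calls 1.4 an assumed rate and gives no source, so this cannot be taken for granted; failing it, show a range of k. State the sidedness of the test and the group to which 1.4 applies.

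Then restate the claim in both the Abstract and the Sample size section, either as the power for a 14% reduction at 352 + 1408 or as the reduction detectable with 80% power at that size (about 17.5% to 24.8% for k=0.5 to 2). Add a sentence that covariate adjustment in a non-randomised comparison may change the precision further.

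The cost is one recalculation and some reworded sentences. No extra patients are needed. The downside is a less favourable stated figure.

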### Statistical analyses

Descriptive statistics will be generated for all socio-demographic and clinical characteristics, and outcome measures. A multivariable Poisson or negative binomial regression (depending on over-dispersion) will be used to determine whether the rates of ED presentations were different between the PROMPT-Care and control groups adjusting for covariates (such as age, sex, stage of disease, and treatment status). Number of referrals to allied health services will be analysed similarly. Multivariable Cox proportional hazards model will be used to analyse length of time from start to end of chemotherapy adjusting for covariates.

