### Control population

A list of potential control individuals (minimum *n* = 1408) will be extracted from hospital databases of the general cancer patient population who were seen at the participating cancer therapy centres during the study period.

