#### Patient identification and consent

Participating clinicians will review their clinic lists to identify eligible patients who have appointments scheduled within the coming two (2) months. Two patient recruitment approaches will be utilised to achieve a similar proportion of both patients in active treatment and those in follow-up care.

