### Measures

#### Outcomes

The primary outcome is number of emergency department (ED) presentations observed during the study period. Details about ED presentation dates, reason for presentation and any resulting admissions will be extracted from the electronic medical record (EMR) (Table 1).

**Table 1 Tab1:** Primary and secondary outcome data collected

Data	Description of data	Source of data
Primary Outcomes		
Emergency Department (ED) presentations	• ED presentations (date, number of visits) • Length of stay • Reason for presentation	Extracted from electronic medical record (EMR)
Secondary Outcomes		
Time on chemotherapy	• Planned chemotherapy regimen • Actual regimen start and end date • Toxicities, changes to treatment delivery and reasons	Extracted from oncology information system (OIS)
Referral to allied health services	• Date of referral and allied health service type • Reason for referral eg. emotional distress, case management etc.	Extracted from EMR & OIS

The secondary outcomes are time receiving active chemotherapy and referrals to allied health services. Details of planned and actual chemotherapy regimens as well as any toxicities and changes to treatment delivery will be extracted from the OIS. Date, reason and number of referrals to allied health services will be tabulated and extracted from the medical record and OIS.

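### The primary count model, read in the ordinary way, applies one dispersion to two differently assembled arms at 1:4, so its interval and p-value are miscalibrated if residual dispersion differs by arm; pre-set robust standard errors are a cheap safeguard

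*Protocol article*

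**What the plan says.** The outcome is a count. Protocol article, Outcomes: "The primary outcome is number of emergency department (ED) presentations observed during the study period".

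The primary analysis is in Statistical analyses: "A multivariable Poisson or negative binomial regression (depending on over-dispersion) will be used", "adjusting for covariates (such as age, sex, stage of disease, and treatment status"). The following sentence extends the method to a secondary outcome: "Number of referrals to allied health services will be analysed similarly". The model is thus picked "depending on over-dispersion", but the article does not name the over-dispersion check, the form of the dispersion parameter or the type of standard error.

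The arms come from different processes. Intervention patients are identified by participating clinicians and give consent. They must manage the survey in English, have Internet access outside the clinic and not have a blood cancer (Study population, Patients). They are recruited by two routes "to achieve a similar proportion of both patients in active treatment and those in follow-up care". Controls are "extracted from hospital databases of the general cancer patient population who were seen at the participating cancer therapy centres during the study period", and the Control population section repeats none of those restrictions.

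The Sample size section gives 352 intervention and 1408 control patients, 1.4 visits per patient, a 14% reduction, and "80% power and 5% statistical significance".

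**The concern.** The choice between Poisson and negative binomial matters chiefly when the standard errors are taken from the fitted model. Poisson ties the variance to the mean. Ordinary negative binomial regression adds one dispersion parameter for all patients. With four controls per intervention patient, the controls dominate the estimate of that parameter, yet the smaller arm contributes most of the variance of the rate ratio. A dispersion that is wrong for the intervention arm therefore does most harm where the standard error is most sensitive to it.

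In a randomised trial, equal residual dispersion under the null follows from the design. Here the arms are formed by consent and by database extraction, so it does not. What is at stake is the coverage of the primary interval and the size of the primary test, and likewise for referral counts.

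**Working it through.** **1. Inputs.** From Sample size: 352 and 1408 patients, control mean 1.4, rate ratio 0.86 (intervention mean 1.204), 5%, 80%. The article gives no dispersion, so every dispersion k below (variance = mean + k × mean²) is an assumption.

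**2. The plan's own figure.** Wald test on the log rate ratio, Poisson variance, two-sided:

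n = (1.960 + 0.842)² × (1/1.204 + 1/(4 × 1.4)) / (ln 0.86)² = 348.2, so 349 intervention patients and 1745 in total. The plan states 352 and 1760, within 1%. The sample size is therefore reproduced with no over-dispersion.

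**3. Which arm drives the variance.** Poisson at the design rates: 1/(352 × 1.204) = 0.00236 and 1/(1408 × 1.4) = 0.00051, total 0.00287. The intervention share is 0.00236/0.00287 = 82%. With equal means and equal k it is (1/352)/(1/352 + 1/1408) = 80%.

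**4. Analytic size under the null (both means 1.4).** Approximate the common dispersion as k = 0.2 × k_int + 0.8 × k_con.

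- True variance: (1/1.4 + k_int)/352 + (1/1.4 + k_con)/1408
- Model variance: (1/1.4 + k) × (1/352 + 1/1408)
- Size: 2 × [1 − Φ(1.96 × √(model/true))]

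For 2/1: k = 1.2; true = 2.714/352 + 1.714/1408 = 0.0089; model = 1.914 × 0.00355 = 0.0068; size 8.7%.

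**5. Simulation.** 352 against 1408, mean 1.4, equal follow-up, no covariates, 8000 null runs per setting. A likelihood-ratio check chose between Poisson and common-dispersion negative binomial. The Monte Carlo standard error near 5% is √(0.05 × 0.95/8000) = 0.24 points.

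| k, intervention/control | Analytic | Model-based | Robust |
|---|---|---|---|
| 0.5/0.5 | 5.0% | 5.0% | 4.9% |
| 1/1 | 5.0% | 5.4% | 5.6% |
| 1.25/1 | 6.0% | 6.1% | 5.3% |
| 1.5/1 | 6.9% | 6.9% | 5.2% |
| 1/0.5 | 7.7% | 7.9% | 5.5% |
| 2/1 | 8.7% | 8.7% | 5.1% |
| 0.5/1 | 3.0% | 3.1% | 5.0% |
| 1/2 | 2.5% | 2.5% | 4.9% |

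Repeat simulations gave 8.8-9.4% (2/1), 7.2-7.5% (1/0.5), 6.2% (1.25/1), 2.6-2.7% (1/2) and 2.7-3.0% (0.5/1). With follow-up varying from 4 to 20 months (an assumption; the article states only a four-month minimum; 2500 runs), the model-based negative binomial gave 9.6% (2/1) and 3.0% (1/2). Negative binomial with robust errors gave 5.2-6.1%.

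**6. The switch on its own.** With equal dispersion and the likelihood-ratio check, the two-stage test has size 4.7-5.4%. At k = 0.1 the negative binomial is chosen in about 98% of runs. Harm would need a lenient check that kept Poisson despite over-dispersion: 2 × [1 − Φ(1.96/√v)] gives 8.0% at a variance/mean ratio v of 1.25 and 16.6% at 2.

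**7. What robust errors cannot do.** With k = 1 in both arms and no true effect, residual confounding equal to a rate ratio of 0.95 gives 10% rejection, and of 0.90 gives 27%, even with a correct variance.

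**The case against.** The strongest reply is that the article states neither a common dispersion nor model-based standard errors. It is a condensed account, and an analysis plan that is not shown may settle the check, the parameterisation and the variance estimator. This stands as a limit: the fault lies in the ordinary reading of the sentence, not in its words, and silence on those details is not the complaint. But the sentence does fix a method that leans on the variance model, and that method suits this allocation and this way of forming the arms poorly.

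Next, the sizes rest on assumed dispersion ratios in simulations without covariates. This also stands. Treatment status is among the example covariates, so adjustment may absorb part of the difference in case mix, including the part produced by the recruitment target.

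Three stronger readings are tempting and are not supported:

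- A reader might infer that choosing the model from the data inflates the error. With a formal check it does not (step 6).
- A reader might infer that the primary test is anti-conservative. Nothing in the article says which arm is more variable. The control description is the broader one, which if anything points to the conservative side.
- A reader might infer that robust errors secure a 5% error rate. In a non-randomised comparison they correct the variance only (step 7).

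**Conclusion.** The point holds as a conditional one. If residual dispersion differs by arm, and the standard errors come from a common-dispersion model, the primary test departs from its nominal level by about 1 to 4 points upward, or 2 to 2.5 points downward, over the ratios examined. The 1:4 allocation makes this worse. If dispersions are equal after adjustment, nothing is wrong. The article gives no data to say which case applies. The size depends on the assumed dispersions, the mean of 1.4, the absence of covariates and the ordinary reading of the model. This is a worthwhile safeguard for the primary interval, not proof that the planned test fails.

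**What to change.** In Statistical analyses, replace the over-dispersion switch with one model set before outcome data are examined: negative binomial regression with log link and the planned covariates, with the primary confidence interval and test taken from heteroscedasticity-robust (sandwich) standard errors. Letting the dispersion differ by arm is an acceptable alternative. State that referral counts follow the same rule.

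The cost is one sentence and one software option, with no extra patients or data. At the planned effect, power (robust against model-based negative binomial) is practically unchanged when dispersions are equal: 60.3% against 60.3% at k = 0.5, 48.9% against 48.7% at k = 1, and 33.6% against 33.4% at k = 2. Where dispersions differ it moves either way: 35.1% against 45.5% at 2/1, where the higher figure belongs to a test with inflated size, and 43.4% against 33.0% at 1/2. Confounding between the arms needs its own handling and is untouched by this change.
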